## Abstract

Acquiring movement skills is crucial across the lifespan, supporting an individual’s participation in sports and physical activities. Errorless motor learning, which promotes success during practice, has been shown to be effective for acquiring or reacquiring (e.g., following injury/disease) movement skills. This research explores the underlying processes of errorless motor learning in children and older adults. We will investigate two distinct processes associated with motor learning: (i) cognitive processing measured by movement variability and prefrontal cortex (PFC) activity and (ii) affective processing measured by perceived competence. We will recruit two participant groups—children, and older adults—who will practice a novel throwing task in either a condition where errors are minimized or a condition where errors freely occur. We will measure task performance, movement variability, perceived competence, and PFC activity before, during, and after practice. We will control for individual cognitive abilities (processing speed and executive function) and use hierarchical linear mixed models to compare the variables between the practice conditions and to verify whether the cognitive and affective processes influence outcomes following practice. The findings are expected to contribute to our understanding of skills acquisition across the lifespan and help facilitate the (re)acquisition of motor skills by children and older adults through programs provided by physiotherapists, coaches, teachers, and health professionals. This study has been registered in the Open Science Framework Registries (https://doi.org/10.17605/OSF.IO/YTERV).

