While freely occurring practice errors hamper performance during learning, other research has shown that performance outcomes subsequently improve significantly (Lee et al., 2016), which suggests that errorless motor learning may not necessarily be advantageous. However, a key advantage associated with errorless motor learning is that learners can manage multiple tasks while displaying effective movement performance after the learning phase. This benefit has been shown in studies of children (Capio et al., 2013a, 2013b) and older adults (Chauvel et al., 2012) and may be explained by the relative independence of errorless learning from working memory resources. For instance, children with low working memory capacity showed enhanced learning when they made fewer errors during practice (van Abswoude et al., 2015). With less reliance on cognitive resources, the apparent defining advantage of errorless motor learning lies in the ability to rely on movement skills when individuals need to engage with competing attentional demands (e.g., children in playgrounds who are socializing with others and older adults who are minding environmental constraints during exercise).

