### Outcome measures

2.3

The outcome measures consist of task performance, movement variability, perceived competence, and PFC activity. Covariate measures include cognitive processing speed and executive function capacity.

Task performance during the learning phase is measured by the number of successful hits on the target in each block. Task performance during the test phase is measured by accuracy scores. Task performance scores will be measured in real time by two independent observers and verified *post hoc* using video recordings of the target. The range of scores for successful hits during learning is 0–15 per block, and the ranges for accuracy during the tests are 0–100 per trial and 0–1000 for each test (Capio and Eguia, 2025).

Movement variability will be calculated using the coefficient of variation (CV) of the joint angles and joint velocity. CV is defined as the standard deviation divided by the mean (expressed as a percentage) and provides a normalized measure of how consistently joint kinematics are maintained across repeated movements (Mukherjee and Yentes, 2018). Movement kinematics will be generated using the Noraxon MyoMOTION system (Noraxon Inc., United States), which uses inertial measurement units (IMUs) to track the three-dimensional angular changes in the upper limb used for throwing. This instrument has been shown to provide valid estimates of joint kinematics (Heuvelmans et al., 2025). Four IMUs will be positioned on the (i) dorsum of the hand, (ii) dorsal side of the distal half of the forearm, (iii) lateral side of the middle third of the upper arm, and (iv) over the spine of the upper thoracic region.

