To account for individual cognitive processing speed and executive function capacity, we will use the Color Trails Test (CTT)-1 and -2 (Williams et al., 1995) for children and the Trail Making Test (TMT)-A and -B (Bowie and Harvey, 2006) for older adults. CTT-1 and TMT-A scores are considered measures of visual search and perceptual speed, whereas CTT-2 and TMT-B scores reflect the task-switching component of executive function. For all participants, verbal working memory will be assessed using a backward digit span test (Ramsay and Reynolds, 1995), and visuospatial working memory will be assessed using a reversed Corsi block tapping test (Corsi, 1973).

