We will use random effects multilevel/hierarchical linear model (HLM) analysis to test our hypotheses. To test changes in the learning and test phases, we use the HLM approach to estimate growth curve models to examine change over time (i.e., practice blocks, test) on two levels—level one representing individual change over time and level two accounting for the extent to which change differs between age groups and between the EL and EF groups (Raudenbush and Bryk, 2002). The level one model will quantify individual changes in the measured variables (i.e., task performance, movement variability, perceived competence, PFC activity) as a function of time (i.e., practice block, test). Random slopes and intercepts will be specified for participants to account for individual differences in baseline performance and rate of change. For the level two model, fixed effects will include age group (i.e., children, older adults) and learning condition (i.e., EL, EF) as categorical predictors. Additional fixed effects will include the relevant covariates (i.e., cognitive processing speed and executive function). The random effects of the repeated measures estimate the relationship of the scores at the first time point to the rate of change over time. Planned interactions will include age group × learning condition to examine different effects of the learning condition across age groups and time × learning condition to test whether learning trajectories vary between the EL and EF conditions. Separate models will be fitted to each of the measured variables.

The statistical assumptions underlying HLM (i.e., normality of residuals, homoscedasticity, and independence of random effects) will be evaluated through diagnostic plots and residual analysis. If violations are detected, robust estimation methods or appropriate variable transformations will be applied. Missing data will be handled through maximum likelihood estimation under the assumption of missing at random (MAR) to retain all available data and minimize bias. Our data analysis approach is deemed appropriate because it allows us to track change over repeated measures and account for participants’ individual patterns of change by calculating estimates of within- and between-individual variation (O’Connell and McCoach, 2004).

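### The two working-memory scores have no stated role, and cognitive covariates entered without covariate × time do not adjust the time × condition comparison

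*Protocol article*

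**What the plan says.** The Abstract states: "We will control for individual cognitive abilities (processing speed and executive function". Section 2.3 (Outcome measures) repeats the pair: "Covariate measures include cognitive processing speed and executive function capacity".

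The tests come later in section 2.3. The paragraph opens with "To account for individual cognitive processing speed and executive function capacity, we will use the Color Trails Test (CTT)-1 and -2"; older adults take the Trail Making Test instead. Part 1/A is assigned to visual search and perceptual speed, and for part 2/B the text says that "CTT-2 and TMT-B scores reflect the task-switching component of executive function". The paragraph then adds: "For all participants, verbal working memory will be assessed using a backward digit span test", with a reversed Corsi test for visuospatial working memory.

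Section 2.6 (Data processing and analysis) specifies a two-level growth model with random intercepts and slopes. For level two it says: "Additional fixed effects will include the relevant covariates (i.e., cognitive processing speed and executive function". The interactions it names are age group × condition and time × condition. The hypotheses in section 1.4 are about whether change differs between the errorless and errorful conditions, which is the time × condition term.

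**The concern.** There are two linked problems.

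First, four cognitive scores are collected and two covariates are named. The only scores that the text ties to those two names are the trail-test parts. Working memory is nevertheless the ability that the introduction ties most closely to errorless practice; section 1.2 reports, for example, that "children with low working memory capacity showed enhanced learning when they made fewer errors during practice". The digit span and Corsi tests are also the only cognitive tests given in the same form to both age groups.

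Second, a person-level score entered as a main effect explains differences in level. The hypotheses concern differences in change. If the covariates enter only as listed, the control announced in the Abstract does not reach the contrast that tests those hypotheses. What is at stake is precision, and the ability to correct a chance difference in cognitive ability between arms. With 52 recruited per age group and equal allocation, the arms have 26 and 26 within an age group, or 52 and 52 when both age groups are pooled.

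**Working it through.** **1. The article's own figure.** Section 2.1 gives 46 per age group (effect size 0.23, 80% power, alpha 0.05). The metric of the effect size is not named. Read as f² = 0.23 in an F test of R² increase (noncentrality f² × N, denominator df N − k − 1) with two tested predictors, N = 46 gives power 0.81. With 2 to 7 predictors in total, power stays between 0.810 and 0.806. Attrition: 46 / (1 − 0.10) = 51.1, rounded up to 52. Both figures reproduce, and extra covariates hardly move them. This point does not change the sample size.

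**2. Scores against named covariates.**

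| Score (section 2.3) | Ability the text assigns | Named as covariate? |
|---|---|---|
| CTT-1 / TMT-A | perceptual speed | yes, processing speed |
| CTT-2 / TMT-B | task switching | yes, executive function |
| Backward digit span | verbal working memory | not by name |
| Reversed Corsi | visuospatial working memory | not by name |

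**3. Why a main effect does not reach time × condition.** Write the model for participant i as intercept aᵢ and slope bᵢ, with condition c and covariate w:

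- level two as listed: aᵢ = α₀ + α₁cᵢ + α₂wᵢ + uᵢ; bᵢ = β₀ + β₁cᵢ + vᵢ
- with covariate × time: bᵢ = β₀ + β₁cᵢ + β₂wᵢ + vᵢ

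Time × condition is β₁. With the same time points for everyone and no gaps, each participant's slope is a contrast across occasions from which the constant α₂wᵢ cancels. Every predictor in the slope equation is also in the intercept equation, so generalised least squares returns the ordinary comparison of mean slopes for β₁, whatever the correlation of uᵢ and vᵢ. Adding w to the intercept alone changes neither the estimate of β₁ nor its standard error (SE).

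This treats the cognitive scores as measured once per participant. The text gives no repeat schedule for them.

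**4. Numerical check.** Growth models with random intercept and slope were fitted by maximum likelihood to simulated data: 104 participants, 6 time points, a covariate related to both level and slope, 20 data sets per row. All settings are assumed. The SE columns refer to time × condition.

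| Observations missing | Mean (max) shift in estimate from adding covariate main effect | SE, no covariate | SE, main effect | SE, covariate × time |
|---|---|---|---|---|
| 0% | 0 (at most 7e-15) | 0.1385 | 0.1385 | 0.1272 |
| 10% | 0.004 (0.010) | 0.1450 | 0.1451 | 0.1325 |
| 30% | 0.008 (0.037) | 0.1454 | 0.1459 | 0.1347 |

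With complete data, covariate × time reduces the SE by 1 − 0.1272/0.1385 = 8%. It moves the estimate by 0.049 on average (maximum 0.141), which is the adjustment for chance imbalance.

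A second illustration (92 participants, 4 occasions, one simulated data set) gave an estimate of 0.0853 with SE 0.0636, both without the covariate and with its main effect. With covariate × time it gave 0.0889 with SE 0.0554, a reduction of 1 − 0.0554/0.0636 = 13%.

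**5. What main effects do achieve.** In the complete-data runs of step 4, the covariate main effect cut the SE of the condition term from 0.394 to 0.306 and that of age group × condition from 0.545 to 0.432.

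**6. Dependence on the assumed correlation.** If the covariate correlates r with observed individual change, the variance of the slope contrast is multiplied by about 1 − r² and the SE by √(1 − r²).

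| r (assumed) | Variance reduction | SE reduction | Equivalent extra participants, 1/(1 − r²) − 1 |
|---|---|---|---|
| 0.2 | 4% | 2% | 4% |
| 0.3 | 9% | 5% | 10% |
| 0.4 | 16% | 8% | 19% |
| 0.5 | 25% | 13% | 33% |

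The two simulations therefore correspond to r of about 0.4 and 0.5. A weaker relation would give less.

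**The case against.** The strongest reply is that the article condenses a fuller plan and can be read without contradiction. The span tests sit in a paragraph whose stated purpose is to account for processing speed and executive function, and task switching is called one component of executive function, so working memory may be another. A reader might infer that working memory has been dropped from the analysis; the text does not establish that. The Abstract also never promises control for working memory by name. This part of the reply stands, and what remains is that the article does not say which scores make up the covariates.

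Similarly, the list of interactions is not worded as complete. Level two is described as explaining differences in change, and age group × time is unlisted although change is said to differ by age group. So covariate × time is not excluded. But section 2.6 does set out how the covariates enter and which interactions are planned, and nothing in it puts a covariate into the slope.

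A reader might also infer that the covariates are useless. Step 5 of the working shows otherwise: they sharpen age group × condition, one of the two planned interactions. Exact invariance of time × condition also needs complete balanced data, whereas section 2.6 plans maximum likelihood under missing at random. The resulting shifts are small and bring no gain in SE.

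Finally, the size of the gain rests on assumed correlations. By the article's own theory working memory matters mainly under errorful practice, so one common covariate × time slope for both arms is a simplification. That limits the expected gain but does not make the main-effects model the better one.

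**Conclusion.** The point holds in a limited form. The two working-memory scores have no stated analytic role unless they are counted under executive function. Covariates entered as section 2.6 lists them do not adjust the time × condition comparison: the effect is exactly nil with complete balanced data and negligible at 10% to 30% missing observations.

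The stronger inference, that the comparison of conditions is biased, is not supported. Condition is randomised, so the loss is precision and adjustment for chance imbalance. The 8% and 13% reductions in SE are illustrations under assumed relations between covariate and change. The nil effect of a main-effect covariate does not depend on those assumptions; it needs only a covariate that is constant over time and a common, complete measurement schedule. This is a worthwhile, inexpensive improvement and not a threat to the validity of the trial.

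**What to change.** In sections 2.3 and 2.6, state that the backward digit span and reversed Corsi scores are level-two covariates, alongside the trail-test scores. In section 2.6, enter the baseline cognitive covariates, centred within age group, as predictors of both the intercept and the slope, by adding covariate × time to the planned terms. Record this before the data are analysed.

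The cost is wording and a few more model terms in 92 to 104 participants; all the scores are already planned. A working memory × condition × time term would examine the article's idea that low-capacity learners gain most from errorless practice. It is not among the section 1.4 hypotheses and no power is shown for it, so it should be at most an optional exploratory analysis.

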Recruitment of participants will be conducted by research assistants through public announcements on the social media pages of the university and nearby communities. Interested participants will be able to contact the research team directly through online messaging (i.e., WhatsApp) and will be scheduled for screening and experiment participation. Informed consent and verbal assent (for children) will be obtained by the research assistants. Within each age group, participants will be randomly assigned in equal numbers by sex to either the errorless (EL) or errorful (EF) group via stratified block randomization. The random allocation block sequence will be computer-generated by research staff not involved in participant recruitment or assignment.

Participants will be informed only about the procedures and requirements of the group to which they were allocated and without knowledge that an alternative condition exists. Due to the nature of the study procedures, research staff will be aware of group assignment for protocol implementation. Thus, while participant blinding is implemented to the extent possible, research staff cannot be blinded, and this limitation is acknowledged as inherent to the study design.

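### The fixed-effect list omits sex, the stratification factor, and the pretest value in the learning-phase models; this costs precision for level contrasts but does not bias errorless versus errorful

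*Protocol article*

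**What the plan says.** **Model terms** (Protocol article, Data processing and analysis, 2.6). One model per measured variable covers both age groups: "fixed effects will include age group (i.e., children, older adults) and learning condition (i.e., EL, EF) as categorical predictors". The covariates follow: "Additional fixed effects will include the relevant covariates (i.e., cognitive processing speed and executive function". The interactions are time × learning condition and one without time: "Planned interactions will include age group × learning condition to examine different effects of the learning condition across age groups". Baseline differences are left to the random effects: "Random slopes and intercepts will be specified for participants to account for individual differences in baseline performance and rate of change". Sex, a pretest covariate and an age group × covariate term are not named.

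**Randomisation** (Participants and eligibility criteria, 2.1). Children and older adults are allocated separately, with sex as the stratum: "participants will be randomly assigned in equal numbers by sex to either the errorless (EL) or errorful (EF) group via stratified block randomization".

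**Timing and scales** (Study setting and procedures, 2.2; Outcome measures, 2.3). Movement kinematics and PFC activity are recorded at pretest, in blocks three to eight of each session, and at posttest. Perceived competence is taken after the pretest, after blocks three and eight of each session, and after the posttest. Task performance is counted as hits (0–15) per practice block but as an accuracy score (0–1000) in the tests.

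**Trail tests** (Outcome measures, 2.3). For children "we will use the Color Trails Test (CTT)-1 and -2"; older adults take "the Trail Making Test (TMT)-A and -B". The article treats the two tests as measuring the same constructs: "CTT-1 and TMT-A scores are considered measures of visual search and perceptual speed".

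**The concern.** A factor that restricts the randomisation normally belongs in the analysis model. Otherwise the variance that the design has balanced out stays in the residual, and the model-based standard error is larger than the real sampling error.

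The random intercept in the learning-phase models is not a substitute for a pretest covariate. Under the schedule in 2.2, block 1 is thrown at a 100 cm radius in EL and 10 cm in EF. By block 3, where kinematics and PFC recording begins, the radii are 90 cm and 10 cm. The first time point therefore already reflects the condition. A same-scale pretest exists for three of the four outcomes and is not used in these models.

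At stake is precision for any contrast of levels: the condition main effect and the planned age group × condition interaction. A lesser issue is that two different instruments feed one covariate in a model that pools the age groups.

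**Working it through.** **Plan's own figure.** Inputs from 2.1: effect size 0.23, 80% power, alpha 0.05, 46 per age group. The metric is not named. Read as f² in a test of R² increase (noncentral F, λ = f²N, u tested predictors, p predictors in total), u = 2 gives N = 46 with power 0.81. This holds for p = 2 to 6, so extra covariates in that range do not change N. The attrition allowance also reproduces: 46/0.9 = 51.1, rounded up to 52.

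The article gives no variance share for sex and no correlations, so the inputs below are assumed and shown as ranges.

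**Sex omitted.** Allocation is balanced within sex, so sex adds nothing to the true variance of an EL–EF level contrast, but its share R² stays in the estimated residual. The reported SE is too large by 1/√(1 − R²) − 1, and the actual alpha is about 2[1 − Φ(1.96/√(1 − R²))].

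| R² for sex | SE overstated | Actual alpha |
|---|---|---|
| 0.01 | 0.5% | 0.049 |
| 0.05 | 2.6% | 0.044 |
| 0.10 | 5.4% | 0.039 |
| 0.20 | 11.8% | 0.028 |

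**Pretest omitted.** With correlation ρ between the pretest and the practice level, adjustment leaves a fraction 1 − ρ² of the variance. Omission therefore inflates the SE by 1/√(1 − ρ²) − 1.

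| ρ | SE inflation |
|---|---|
| 0.2 | 2% |
| 0.3 | 5% |
| 0.5 | 15% |
| 0.7 | 40% |

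**Simulation of a level contrast.** Inputs: 92 participants, 4000 runs, covariate correlation 0.4, sex R² 0.10, pretest correlation 0.5, trail-score SD ratio 2 between age groups.

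| Model | Type I error | Power at 0.5 SD | SE |
|---|---|---|---|
| As planned | 0.038 | 0.725 | 0.194 |
| + age-specific covariate slopes | 0.036 | 0.728 | 0.193 |
| + sex | 0.048 | 0.769 | 0.181 |
| + pretest | 0.048 | 0.909 | 0.149 |

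The mean estimate was 0.499 in all four models under the 0.5 SD effect, so there is no bias. The last step is larger than 15% because the other terms had already removed variance: √[(1 − 0.16 − 0.10)/(1 − 0.16 − 0.10 − 0.25)] = √(0.74/0.49) = 1.23, close to 0.181/0.149 = 1.21.

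**Time × condition.** In a balanced growth model (92 participants, 20 blocks, random intercept and slope, variance components treated as known), the estimate was identical and its SE was 0.186 in each of three models: the planned covariates, age-specific covariate slopes, and those slopes plus sex and pretest as main effects. Time-constant main effects carry no information about a slope difference when everyone is observed at the same times.

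**Trail tests.** Suppose raw scores share one slope, the within-age SDs have ratio k, and each test correlates with the outcome at r. The shared slope is then r(1 + k)/(1 + k²). At r = −0.5 and k = 3 this is −0.2. Residual variances are 1 − 0.2 + 0.04 = 0.84 and 1 − 0.6 + 0.36 = 0.76, mean 0.80, against 0.75 with separate slopes. The SE inflation is √(0.80/0.75) − 1 = 3.3%. Over r from −0.3 to −0.5 and k from 1 to 3 the range is 0 to 3.3%, with no bias in EL versus EF.

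**The case against.** The strongest reply is that the hypotheses concern differences in change between conditions, tested by time × condition, and that term hardly responds to sex or pretest main effects. This stands for balanced, complete data. It does not cover age group × condition, which 2.6 plans without time and which is a contrast of levels, or a condition main effect. The article also allows for attrition and data loss in 2.1, so exact balance is not assured.

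A second reply is that baseline is already handled. In the test-phase models that is right, because the pretest is itself a time point. In the learning-phase models the random intercept describes a level reached under the assigned condition, so it does not replace the pretest.

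Third, a pretest of the same variable does not exist for task performance. That is correct, and the fix is limited accordingly.

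Fourth, a condensed article may leave covariate scaling to a fuller plan. This is fair for the trail scores: 2.6 does not say whether they enter raw, standardised or age-normed. A reader might infer that the adjusted age-group effect will be a false effect of some definite size. The article does not support that. It gives no means or SDs for either test, and any such figure would come from an assumed gap between the means. None of the hypotheses stated in 1.4 tests the age-group main effect. Backward digit span and reversed Corsi are given to everyone, so the issue is confined to the trail tests. The same defence is weaker for sex, since 2.6 itself states which covariates enter.

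**Conclusion.** The point holds as a loss of efficiency, not as a threat to validity. The stated covariates omit the stratification factor, and the learning-phase models omit an available pretest value.

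A reader might infer that EL versus EF is biased or that false positives are inflated. Neither follows: allocation is randomised within age group, the contrast is unbiased in every version checked, and omitting sex makes the test conservative.

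The costs fall on level contrasts. Alpha is about 0.044 to 0.039 for an assumed 5 to 10% of variance due to sex, and the SE is about 5 to 40% larger for assumed pretest correlations of 0.3 to 0.7. Time × condition is essentially unaffected in balanced, complete data, and the sample size does not change. The conclusion takes the covariate list in 2.6 as complete and the learning-phase time axis as practice blocks only. The trail-test matter is secondary: it affects how the covariate coefficient and the adjusted age-group main effect may be read.

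**What to change.** 1. Add sex as a fixed effect in every model.
2. In the learning-phase models for movement variability, perceived competence and PFC activity, add the pretest value of the same variable as a covariate. For task performance, state whether the pretest accuracy score will be used, noting that its scale differs from hits per block.
3. Enter the trail scores standardised within age group, or give them age-specific slopes. State that the covariate-adjusted age-group main effect will not be interpreted as a comparison of children and older adults at equal cognitive ability.

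The cost is a few model terms and degrees of freedom. Sex and the pretest measures are already part of the design, no procedure changes, and 46 analysed per age group still stands. The change should be recorded before analysis; data gathering is expected to end by June 2026.
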